### 3.4 THEORETICAL AND CONCEPTUAL APPROACH

Phase III, multicenter, randomized, double-blind, controlled clinical trial; The coordinating center will be INER and it is expected to recruit other hospital centers in Mexico City and in other states. Planned to be carried out in critical areas (Emergencies, intensive care, postoperative recovery) and in Hospitalization services of the National Institute of Respiratory Diseases Ismael Cosío Villegas and participating hospitals.

Subjects eligible will be adults over 18 years of age with a confirmed diagnosis of COVID-19 by RT-PCR (in a pharyngeal, nasopharyngeal sample or in a tracheal aspirate / bronchial lavage) that requires hospitalization for severe or critical COVID-19.

1. **Blinding:** Patients who agree to participate, who are hospitalized at INER or collaborating centers, with a diagnosis of severe disease due to COVID-19 will be randomized. The randomization will be centralized, carried out by a dedicated software, and randomization will be utilized to label the experimental drug and the placebo. The treating doctors, the nursing staff and the rest of the treating team and the evaluators of the outcomes will be blinded to the group corresponding to each one of the subjects.

**2. Risk stratification** Subjects included in two groups will be stratified for randomization:

- a. Stratum A: Subjects diagnosed with severe disease by COVID-19 requiring hospitalization that do not require invasive ventilatory management.
- b. Stratum B: Subjects diagnosed with severe disease by COVID-19 requiring invasive ventilatory management and / or management in the intensive care respiratory unit at the time of randomization.

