**3. Main outcome:**

- a. Mortality rate at 30 days after randomization.

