**4. Secondary outcomes:**

- a. Proportion of patients needing invasive ventilatory support (stratum A only)
- b. Duration in days of invasive mechanical ventilation for patients requiring such procedure
- c. Time in days from randomization to hospital discharge.
- d. Time in days from randomization to end of oxygen therapy
- e. Time in days to negative viral test using weekly RT-PCR testing
- f. Incidence of AEs and AEs leading to treatment discontinuation
- g. • Incidence of serious adverse events

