**6. Specific protocol interventions:**

- a. Subjects entering the experimental group will receive hydroxychloroquine orally or by nasogastric tube (refer to the protocol procedures manual for the method of crushing tablets and administration via nasogastric tube), 200 mg every 12 hours, for 10 days. The placebo group will receive an identical placebo for 10 days. 10 days are tentatively proposed although the working groups suggest a use between 5 to 14 days; the box of hydroxychloroquine contains 20 tablets of 200mg; We justify the 10-day period because it is somewhere in between the various recommendations and because it is more practical to use one box per subject
- b. Patients in both strata will be treated according to protocols of participating institution under the responsibility of the physician in charge: all interventions, medications for all purposes, or non-drug interventions will be registered.
- c. Patients will be followed up to 30 days after randomization by telephone if discharge occur earlier than Day 30
- d. The Investigator is responsible for detecting, documenting, and recording events that meet the definition of an AE or SAE and remain responsible for following up AEs that are serious, considered related to the study

intervention or study procedures, or that caused the participant to discontinue the study

- e. Adverse events will be reported to CE and to manufacturer of the drug (Sanofi México, S.A. de C.V.)

**Statistical analysis:** The analysis will be carried out in R-Rstudio statistical software. Descriptive statistics will be used according to the type of variable and distribution.

The main outcomes will be compared using parametric and non-parametric tests according to the type of variable and distribution.

Death rate (at 30 days), the primary outcome, will be compared between treatment groups using a logistic regression model, adjusting for age, time from onset of symptoms to randomization, comorbidities (diabetes, hypertension, obesity, tobacco smoking) taking into account the randomization strata.

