From the secondary endpoints, proportion of patients needing mechanical ventilation, will be compared also by a similar logistic regression model as that proposed for 30 days-death rate. Days of mechanical ventilation, days of hospitalization and days of oxygen therapy will be compared in a multivariate model, including an indicator of randomization strata, adjusting for confounding variables (age, time from onset of symptoms to start of treatment, and comorbidities, especially diabetes, obesity, tobacco smoking, hypertension)

We also will compare time to death and time to a negative viral test, adjusting for confounding variables (age, time from onset of symptoms to start of treatment, comorbidities) using the Cox proportional hazards model.

There will be a CMDS, a multidisciplinary advisory group, made up of an expert in statistics, a clinical researcher, an expert in ethics and a clinician related to influenza and coronavirus, none involved in the clinical trial and therefore independent, who in the middle of the Trials will have access to the data and the randomization code to evaluate the data including safety and efficacy results. The study results will remain blinded to trial team and sponsor representatives, so that not to impact final interpretation of the study results.

**Clinical Researcher:** [name], clinical pharmacologist, anesthesiologist and intensivist who will act as coordinator. Dra. [name], Ear nose and Throat specialist and with a masters degree in medical sciences.

**Statistics:** [name], Head of the Department of Epidemiology of INER.

**Ethics:** [name], medical director of INER

**Clinician:** [name], Infectologist, expert in influenza-like infections and now in COVID-19 infection

The aim of the committee is to assess the advantages and disadvantages of continuing the trial in the analysis in the middle of the sample, especially if it is considered ethical to continue the recruitment, given the results found in the middle of the study.

In principle, there are no controlled studies with which to compare but they may appear in the course of the trial.

An interim analysis is planned, upon completing half of the sample, that can identify if a noticeable difference is found in the main outcome measure, demonstrating an advantage in effectiveness, which, due to its magnitude, leads to stopping the trial.

Also, to indicate significant adverse effects or toxicity.

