The final statistical analysis will be carried out taking into account this intermediate analysis. The CMDS will provide a written report (not accessible to anyone outside the CMDS) of its observations. It will be considered sufficient to stop the trial because efficacy in the first interim analysis (1 interim and final), if  $P < 0.0054$  and the final analysis will remain significant with  $p < 0.0492$  (according to O'Brien-Flemming). It can also be stopped if probability of success at the final analysis, given the interim results, is too low.

1. **Sample size:** Mortality reported in severe COVID-19 ranges depending on the source, but in China among hospitalized patients with pneumonia has been reported from 4-15% (1,2,4). The WHO suggests at least 400 subjects for sample estimation in clinical trials evaluating therapies for COVID-19, although severe outcomes or deaths increase considerably in hospitalized patients or those in intensive care as those eligible for this trial. (3). At the moment, many behavioral characteristics and outcomes of COVID-19 are unknown, especially in our setting; For this reason, we used the estimate of a mortality of around 15% in severe COVID-19 with a 50% reduction in mortality with treatment, obtaining in the sample calculation a number of subjects similar to that recommended by the WHO.

- a. 2-tailed significance level 95, alpha 5%
- b. Potency (1-beta, chance of detection): 80%
- c. Treaties vs. controls 1: 1
- d. Estimated mortality in controls 15%
- e. Estimated mortality in experimental 7.5%, reduction in mortality of 7.5%, which is 50% (RR 0.5).

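### Secondary outcome (a), need for invasive ventilation, has no place for death without intubation; read plainly, such a death is a non-event

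*Protocol*

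**What the plan says.** Protocol section 3.4, item 4 (Secondary outcomes), defines outcome (a) as "Proportion of patients needing invasive ventilatory support (stratum A only"). Item 2 describes stratum A as "Subjects diagnosed with severe disease by COVID-19 requiring hospitalization that do not require invasive ventilatory management". The statistical analysis text after item 6 states the method: "From the secondary endpoints, proportion of patients needing mechanical ventilation, will be compared also by a similar logistic regression model" to the one proposed for 30-day death.

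Death is a separate outcome. Item 3 sets the main outcome as "Mortality rate at 30 days after randomization", and item 6c provides the follow-up: "Patients will be followed up to 30 days after randomization by telephone if discharge occur earlier than Day 30". Outcome (a) itself carries no time horizon. The protocol names no composite with death and no competing-event method for it, and does not say how a death without intubation is coded.

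**The concern.** A logistic model needs a yes or a no for each patient. A stratum A patient who dies without intubation can be entered as an event, entered as a non-event, or left out. The definition counts only ventilation, so the plain reading is a non-event. Specific objective D in section 3.3.1 asks whether the need for ventilatory support falls, so a non-event is a favourable result. Some deaths would then be scored as good outcomes.

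Such deaths are plausible in this trial. Entry criterion (e) requires hypoxemic respiratory failure, and planned control mortality is 15%. Exclusion criterion (b) screens for raised risk of sudden cardiac death, a route to death that could bypass intubation. Item 6b leaves care to each institution's own protocols, so the share of deaths without intubation may also vary by site.

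At stake is the reading of a clinically prominent secondary outcome. An arm with more early deaths could appear to need less ventilation. An arm in which patients survive long enough to be intubated could appear to need more.

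**Working it through.** **The plan's own figures.** The protocol gives no expected rate for outcome (a). Its only relevant figures are the mortality inputs to the sample size: "Estimated mortality in controls 15" per cent, and "Estimated mortality in experimental 7.5%, reduction in mortality of 7.5%, which is 50% (RR 0.5"). The sample size built on them reproduces to within one patient per group. By Kelsey, with mean risk 0.1125, n = (1.960 + 0.842)² × 2 × 0.1125 × 0.8875 / 0.075² = 278.6, so 279 (stated 280). Fleiss gives 278 (stated 279), and 304 with continuity correction (stated 305). The mortality inputs are therefore used consistently; the point below does not depend on the sample size.

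**Identity.** Within an arm, let V be the proportion ventilated, U the proportion who die unventilated, and C the proportion ventilated or dead. Then V = C − U, so

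V(HCQ) − V(control) = [C(HCQ) − C(control)] − [U(HCQ) − U(control)].

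Each percentage point by which unintubated deaths differ between arms moves the ventilation comparison one point away from the ventilation-or-death comparison. This needs no assumed rates.

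**Case 1: the planned mortality benefit.** Inputs:
- d = mortality, 15% control and 7.5% HCQ. These are the protocol's whole-trial figures, applied here to stratum A.
- s = intubation risk among survivors, assumed 15% in both arms.
- u = share of deaths without intubation, assumed equal in both arms, at 10%, 25% or 50%.

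Formulas: V = (1 − d)s + d(1 − u) and C = (1 − d)s + d.

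C control = 0.85 × 0.15 + 0.15 = 27.75%. C HCQ = 0.925 × 0.15 + 0.075 = 21.375%. The risk ratio is 0.77 whatever u is.

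| u | V control | V HCQ | RR, ventilation alone | RR, ventilation or death |
|---|---|---|---|---|
| 10% | 0.1275 + 0.1350 = 26.25% | 0.13875 + 0.06750 = 20.63% | 0.79 | 0.77 |
| 25% | 0.1275 + 0.1125 = 24.00% | 0.13875 + 0.05625 = 19.50% | 0.81 | 0.77 |
| 50% | 0.1275 + 0.0750 = 20.25% | 0.13875 + 0.03750 = 17.63% | 0.87 | 0.77 |

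The effect is diluted because unintubated deaths halve (ratio 0.5), and leaving out a component with a larger benefit than the whole pulls the remainder towards 1. The level depends on s. With s assumed at 30%, ventilation or death is 40.5% vs 35.25% (RR 0.87). Ventilation alone is then 39.0% vs 34.5% (RR 0.88) at u = 10%, and 33.0% vs 31.5% (RR 0.95) at u = 50%. The direction is the same.

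**Case 2: more unintubated deaths on HCQ.** Assumed: control 25% ventilated and 2% dead unventilated, so ventilation or death is 27%. Moving x points from ventilated to dead unventilated in the HCQ arm keeps the composite at 27% in both arms (RR 1.00):
- x = 1: 24/25 = 0.96
- x = 3: 22/25 = 0.88
- x = 5: 20/25 = 0.80

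Here the ventilation outcome shows an apparent benefit where fewer intubations are exactly replaced by deaths.

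**Number of deaths involved.** For every 300 patients at 15% mortality, 300 × 0.15 × u gives 4.5, 11.25 or 22.5 deaths counted as non-events at u = 10%, 25% or 50%.

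**The case against.** **The coding is not stated.** A reader might infer that the protocol scores these deaths as not needing ventilation. It does not say so, and *needing* could be stretched to cover a patient who needed ventilation and died without it. That stands as a limit on the wording. The protocol's own usage points the other way: outcome (b) measures ventilation days in patients who require the procedure, and a duration exists only for those who received it. If the wider meaning is intended, it needs a definition.

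**The rule may sit in a statistical analysis plan.** One may exist and is not at hand. But the protocol itself fixes both the endpoint definition and the model. A later rule counting deaths as events would change the stated outcome, so the protocol is the place to settle it.

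**Mortality is the primary outcome.** Excess deaths would show there, and time to death is also compared by a Cox model. This stands: it makes an undetected misreading less likely and limits the seriousness. It does not make outcome (a) interpretable by itself.

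**The outcome as written can be defended.** The proportion ventilated by a fixed day, with death as a competing event, is a legitimate quantity and matches objective D. Ventilation or death answers a somewhat different question and overlaps the primary. This also stands, but the quantity can be read safely only with a fixed horizon and with deaths without ventilation shown beside it. The protocol provides neither.

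**Bias in favour of HCQ.** A reader might infer this from Case 2 alone. The documents do not support it: under the protocol's own planning mortality, with the same share of deaths unintubated in each arm, the distortion runs against HCQ. Nor does the protocol propose dropping these patients.

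**Conclusion.** The concern holds in a limited form. Outcome (a) combines a yes/no definition with a logistic model, leaves no place for death without intubation, and has no time horizon. On a plain reading, unintubated deaths become non-events and the comparison shifts by the between-arm difference in such deaths.

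The direction depends on the data. With planned mortality of 15% vs 7.5%, 15% intubation among survivors and 10% to 50% of deaths unintubated, ventilation alone gives RR 0.79 to 0.87 where ventilation or death gives 0.77. At the low end of that range the gap is small. With an assumed excess of 1 to 5 points of unintubated deaths on HCQ, offset by fewer intubations, it gives RR 0.96 to 0.80 where ventilation or death shows no difference.

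The protocol gives neither the share of deaths without intubation nor the intubation rate, so the actual size is unknown. Whole-trial mortality was applied to stratum A. Section 3.1 places the higher fatality among intensive-care and ventilated patients, so stratum A mortality is probably lower and the effect smaller. The outcome is secondary, and the primary partly exposes the problem. It should be corrected, but it does not threaten the main conclusion of the trial.

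**What to change.** Define outcome (a) as invasive mechanical ventilation or death by day 30 after randomization, in stratum A, using the logistic model with the covariates already listed. Report ventilation and death without ventilation separately by arm. Keep the population at stratum A: changing it to all patients not invasively ventilated at randomization could bring in stratum B patients who are in intensive care but not ventilated.

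If the sponsor prefers to keep ventilation as the outcome, the protocol should say that death without ventilation is a competing event, fix the day-30 horizon, and still show both components by arm.

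The cost is a wording change made before unblinding. Interventions are already registered under item 6b, and 30-day vital status is needed for the primary outcome. For patients discharged before day 30, the telephone contact should also establish whether ventilation took place after discharge. The downside is that the composite overlaps the primary outcome and is partly driven by mortality, which is why the components must be shown.

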#### 3.3.1 SPECIFIC OBJECTIVES

- A) Assess whether days of hospitalization are decreased with HCQ compared to placebo.
- B) Assess whether days of supplemental oxygen therapy are decreased with HCQ compared with placebo.
- C) Assess whether the days for viral test negative (one per week) decrease with HCQ compared with placebo
- D) Assess if the need of ventilatory support with HCQ is decreased compared with placebo.
- E) Assess if the days of mechanical ventilation in patients treated with HCQ decrease compared with placebo.
- D) Evaluate the safety of HCQ.

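### Days of ventilation, hospital stay and oxygen are compared as day counts with no rule for death, so a difference in mortality can distort three secondary outcomes

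*Protocol*

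**What the plan says.** Section 3.3.1 sets the direction of benefit. Objective A reads "Assess whether days of hospitalization are decreased with HCQ compared to placebo", and objectives B and E say the same of oxygen therapy and mechanical ventilation.

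Section 3.4, item 4, defines the outcomes:
- Outcome b concerns ventilation and is worded as "Duration in days of invasive mechanical ventilation for patients requiring such procedure", so it covers only part of the randomised population.
- Outcome c concerns hospital stay and is worded as "Time in days from randomization to hospital discharge", with nothing said of patients who never leave alive.
- Outcome d takes the same form as c, counted to the stopping of oxygen.

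The statistical analysis text in section 3.4 then states: "Days of mechanical ventilation, days of hospitalization and days of oxygen therapy will be compared in a multivariate model". The model includes an indicator of randomisation stratum and adjusts for age, time since symptom onset and comorbidities. Its type is not named. The next sentence gives the Cox model to two other endpoints: "We also will compare time to death and time to a negative viral test, adjusting for confounding variables".

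For b, c and d the protocol mentions no free-day measure, competing event or worst-value rule for patients who die. Death by day 30 is the primary outcome. The sample-size item plans 15% on control and 7.5% on HCQ, and section 3.1 puts mortality at 20-30% in patients needing intensive care and ventilation.

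**The concern.** A patient who dies in hospital has no discharge date, and a patient who dies on oxygen has no end-of-oxygen date in the sense the outcome intends. A model for a number of days must still do something with these patients. There are two obvious options, and neither gives a fair randomised comparison when mortality differs.

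- **Deaths counted at their date.** An early death enters as a short stay, which the objectives read as benefit.
- **Deaths dropped.** The comparison is among survivors, a group defined after randomisation. Adjusting for baseline covariates does not restore the balance that randomisation gave.

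Outcome b has a further problem. Stratum A patients are not invasively ventilated at entry, and their later need for ventilation is itself outcome a. If treatment changes who is intubated, it changes who enters the comparison of ventilation days.

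The outcome most worth guarding against is a drug that raises mortality and is then reported to shorten hospital stay. The opposite error, a drug that saves lives and appears to lengthen stay, is equally possible.

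**Working it through.** **1. The plan's own figure.** The protocol gives no calculation for the durations, only for mortality. With 15% v 7.5%, two-sided alpha 5% and power 80%, the Kelsey formula is 2 x 0.1125 x 0.8875 x 7.849 / 0.075² = 278.6, so 279 per group (stated 280). Fleiss gives 278 (stated 279), and with continuity correction 304 (stated 305). The stated figures reproduce to within one patient. At the chosen 300 per group, power is 83.0%. The mortality inputs can therefore be carried forward.

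**2. Deaths counted at their date.** Let p be an arm's mortality. S and D are assumptions. Suppose treatment has no effect on survivors' course, so S and D are the same in both arms.

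Arm mean = (1 - p) x S + p x D

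HCQ minus control = (pC - pT) x (S - D) = 0.075 x (S - D)

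With S = 15 and D = 8:
- control: 0.85 x 15 + 0.15 x 8 = 13.95 days
- HCQ: 0.925 x 15 + 0.075 x 8 = 14.475 days
- difference: 0.525 days longer on HCQ, although survivors' courses are identical

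Range over S = 12 to 20 and D = 5 to 10: from 0.075 x (12 - 10) = 0.15 to 0.075 x (20 - 5) = 1.125 days. A separate simulation capped at day 30, with S = 15 to 20 and D = 8 to 10, gave 0.4 to 0.8 days.

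At the top of the intensive-care range, with an assumed halving (30% v 15%), the shift is 0.15 x (S - D): 1.05 days at S = 15 and D = 8, range 0.30 to 2.25.

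**3. Dependence on the timing of death.** If D = S the shift is zero. If S = 12 and D = 18 it is 0.075 x (-6) = -0.45 days, the opposite direction.

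**4. Effect on inference.** Simulation: 300 per arm, 3,000 trials, gamma-distributed days capped at 30, two-sided t-test at 5%. Unless stated, S = 15 (SD 6) and D = 8 (SD 4), all assumed. About 2.5% is expected on each side by chance.

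| Mortality, control v HCQ | HCQ significantly longer | HCQ significantly shorter |
|---|---|---|
| 15% v 7.5% | 18.1% | 0.2% |
| 7.5% v 15% | 0.1% | 18.9% |
| 30% v 15% | 53.7% | 0.0% |
| 15% v 30% | 0.0% | 52.8% |
| 15% v 15% | 2.5% | 2.7% |
| 15% v 7.5%, D = 15 | 2.5% | 2.4% |
| 15% v 7.5%, S = 12, D = 18 (SD 6) | 0.1% | 14.9% |

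**5. Deaths dropped.** At planned mortality, 300 per arm leaves 300 x 0.85 = 255 control survivors and 300 x 0.925 = 277.5 HCQ survivors. If HCQ only prevents deaths, 22.5 / 277.5 = 8.1% of HCQ survivors are patients who would have died on placebo and have no counterpart among control survivors. The documents do not say how long such patients stay, so the size of this bias cannot be given.

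**6. Free days to day 30, death = 0.** Arm mean = (1 - p) x (30 - S). With S = 15: control 0.85 x 15 = 12.75, HCQ 0.925 x 15 = 13.875, a difference of 1.125 days in favour of the arm with fewer deaths. For S = 12 to 20 the difference is 1.35 down to 0.75. It does not depend on D.

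**The case against.** The strongest reply is that the protocol leaves the rule for deaths open and does not fix a wrong one. The model is unnamed, and outcomes c and d are worded as times from randomisation, which suits a time-to-event analysis. A patient who dies on day 5 has no discharge, so counting that as a five-day stay is a reader's inference. An analysis plan that is not shown may settle it. Part of this stands: the documents do not say that deaths are counted at their date. But the protocol describes the analysed quantities as days, makes fewer days the goal, and names Cox regression only for two other endpoints. Both natural ways of completing that analysis are unsatisfactory. The restriction of outcome b to ventilated patients is explicit and does not depend on any later rule.

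A second reply is that the free-day result above is circular: survivors' courses were set equal, so the difference is only the mortality effect. That is correct. Free days combine survival and duration and do not isolate duration. Their merit is that every randomised patient is included and a death cannot count as a gain.

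Three stronger readings are tempting, and the documents do not support them.
- A reader might infer that the plan necessarily works against HCQ if it saves lives. The sign depends on deaths preceding survivors' discharge, and the documents give no timing for either.
- A reader might infer that the Cox model for time to a negative viral test has the same error. Censoring at death estimates a cause-specific hazard, a recognised choice that misleads only if read as the probability of becoming negative. The protocol does not say how deaths are handled there, and keeping them at risk to day 30 would be compatible with its text.
- A reader might infer that the trial's main conclusion is at risk. The 30-day mortality analysis, its sample size and the efficacy stopping rule do not use these durations.

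**Conclusion.** The concern holds for outcomes b, c and d, as a should-fix point.

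Under the protocol's own mortality assumptions, counting deaths at their date shifts mean days by 0.075 x (S - D). The size, and the 18% rate of significant results in the misleading direction, rest on assumed means and SDs and on no treatment effect in survivors. The figures are best read as hospital days; for ventilation or oxygen the same formula applies with that outcome's own S and D.

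Two parts need no assumption about timing. Dropping deaths gives a non-randomised comparison of survivors, and outcome b in stratum A is conditioned on an event that treatment may change.

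**What to change.** - **Outcome b.** Replace it with ventilator-free days to day 30 in all randomised patients, with death by day 30 scored 0. Report ventilation duration only descriptively, or for patients already ventilated at randomisation. Define that group by ventilation status and not by stratum, because stratum B also admits patients in intensive care on other grounds.
- **Outcomes c and d.** Analyse time to discharge and time to end of oxygen as time to event to day 30, with death as a competing event. Either keep patients who die in the risk set to day 30 as not discharged or still on oxygen, or use cumulative incidence with a Fine-Gray model. Adjust for the randomisation stratum. Patients still in hospital or on oxygen at day 30 are then censored there.
- **Reporting.** Show mortality and duration beside each of these results.

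Outcome e needs no correction on this ground.

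The cost is wording, settled before unblinding. Outcomes a to d already require the dates of ventilation, discharge and end of oxygen, and 30-day vital status is the primary outcome, so no new data are needed. The downside is that free days mix survival with duration, which is why both components should be reported alongside.

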### **3. DESCRIPTION OF THE PROJECT**

#### **3.1 INTRODUCTION AND BACKGROUND**

The outbreak of respiratory infection by the coronavirus 2019 (SARSCOV-2) started in December 2019, in Wuhan City, Hubei Province (China) [1-5]. From this city, the outbreak has been spreading to various provinces of China and other countries [6]. As of February 16, 2020, 28 countries had been recognized with confirmed cases, with 70,548 infections and 1,770 deaths in China, and 413 infections in Japan. [6]. By March 24, > 190 Countries have been affected.

As in other coronaviruses, SARS and MERS, the original human infection was probably obtained from contact with animals, but effective human-to-human transmission has been demonstrated, with a growth rate greater than 1, estimated in 2.6[7], and a rapid duplication of cases that ensure not only the maintenance of the epidemic but also its expansion.

Until now, there is no effective treatment available for COVID-19, however the in-vitro effectiveness of Remdesivir and chloroquine was recently reported, the latter in concentrations capable of being obtained in in-vivo patients who use it [8]. Chloroquine and hydroxychloroquine are originally antimalarial drugs. They have had regular use for decades with a well documented benefit/risk profile, at a very low cost, and if they are proven effective in vivo, they could be very useful drugs. The broad antiviral effect has been attributed to increased pH of endosomes, which are required for virus-cell fusion and also by interference with glycosylation of SARS-VOC cell receptors.[9-11] In addition to the antiviral effect, immunomodulatory effects have been found that could enhance the antiviral effect and the systemic impact of serious infections.

The range of 2019-CoV clinical presentations is wide, from asymptomatic infections to fatal infections, with severe lung damage, respiratory failure, and multi-organ failure. As in severe influenza, severe damage has been associated with a systemic inflammatory reaction or cytokine storm, which could be attenuated by the immunomodulatory and anti-inflammatory effect of chloroquine or hydroxychloroquine.

The overall fatality rate of COVID-19 disease has been estimated at around 2.3%, but in severe cases of respiratory failure, requiring hospitalization or critical care, it is considerably higher, between 10-15%, but could easily increase to 20-30% in those requiring intensive care and mechanical ventilation.

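### Days in hospital, on oxygen and on ventilation are compared as quantities with no place for death or for stays past day 30, so a mortality difference can bias them in a direction set by when deaths occur

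*Protocol*

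**What the plan says.** Protocol section 3.4, Secondary outcomes, defines items c and d as event times: "Time in days from randomization to hospital discharge" and "Time in days from randomization to end of oxygen therapy". Item b is the duration of invasive ventilation in patients who need it.

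The statistical analysis paragraph of section 3.4 handles these outcomes on a day scale. After ventilation days it continues: "days of hospitalization and days of oxygen therapy will be compared in a multivariate model", with an indicator for stratum and adjustment for age, symptom duration and comorbidities. The model type is not named. The next paragraph begins "We also will compare time to death and time to a negative viral test" and assigns those two outcomes to a Cox model.

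Section 3.3.1 sets the direction of benefit: "Assess whether days of hospitalization are decreased with HCQ compared to placebo". Follow-up ends 30 days after randomization.

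The protocol expects many deaths. The sample size rests on 15% mortality in controls and on "Estimated mortality in experimental 7.5%, reduction in mortality of 7.5%, which is 50% (RR 0.5"). The introduction says that mortality "could easily increase to 20-30% in those requiring intensive care and mechanical ventilation", and stratum B enrols such patients. No sentence says how a patient who dies before discharge, on oxygen or on a ventilator enters the day-based comparisons, or how a stay still running at day 30 is counted.

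**The concern.** A patient who dies in hospital never reaches discharge alive. A model of days therefore needs a rule for that patient, and none is given. Run as written, it leaves two natural choices. The count can stop at death, so that an early death looks like a short stay. Or the patient can be left out, which restricts the comparison to survivors, a group selected after randomization. With either choice, an effect on mortality can appear as an effect on days. A stay cut off at day 30 raises a similar problem, because it may be entered as if it had ended.

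Under the planning assumptions about 0.15 x 300 = 45 control patients and 0.075 x 300 = 22.5 treated patients die, so the problem is neither rare nor balanced between arms. Objectives A, B and E read fewer days as benefit. If deaths come early, that scale would count against a drug that saves lives and in favour of one that costs lives.

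**Working it through.** **The plan's own figure.** The protocol gives no figure for days, only a sample size for mortality. With p1 = 0.15, p2 = 0.075, two-sided alpha 0.05, power 80% and 1:1 allocation:

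- Kelsey: (1.960 + 0.842)² x 2 x 0.1125 x 0.8875 / 0.075² = 278.6, so 279 (stated 280).
- Fleiss: 278 (stated 279). With continuity correction: 304 (stated 305).

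Each is within one patient of the stated value. Power at 300 per group is 83.0%. The mortality inputs are therefore the ones the trial is built on.

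**Inputs for the day comparison.** Mortality of 15% and 7.5% comes from the protocol. The rest is assumed, because the protocol gives no timing of death or discharge:

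- S = 14 days: mean stay of patients who would survive in either arm, with no drug effect on it.
- D: mean day of death, varied.
- L: mean stay of patients whom the drug saves, varied.

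**Formulas (treated minus control).**

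1. Days counted to death: control mean = 0.85S + 0.15D; treated mean = 0.85S + 0.075L + 0.075D. Difference = 0.075 x (L - D).
2. Survivors only: (0.85S + 0.075L)/0.925 - S = 0.075 x (L - S)/0.925.
3. Deaths scored as 30 days: 0.075 x (L - 30).

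| D | L | Counted to death | Survivors only | Death = 30 days |
|---|---|---|---|---|
| 8 | 14 | +0.45 | 0.00 | -1.20 |
| 8 | 20 | +0.90 | +0.49 | -0.75 |
| 8 | 28 | +1.50 | +1.14 | -0.15 |
| 20 | 20 | 0.00 | +0.49 | -0.75 |
| 20 | 14 | -0.45 | 0.00 | -1.20 |

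A plus sign means that the life-saving drug appears to lengthen stay.

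**Does a shift of this size reach significance?** Trials with 300 per arm were simulated: gamma stays with a coefficient of variation of 0.5 (assumed), capped at day 30, unadjusted t-test on days counted to death, 1,500 runs per setting. The nominal rate in either direction is 2.5%.

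- D = 8: significantly longer on the life-saving drug in 13% (L = 14), 28% (L = 20) and 46% (L = 25) of trials.
- Harmful drug with 22.5% mortality (assumed), D = 8: significantly shorter in 12%, 31% and 48%.
- D = 14, L = 14: about 2% in each direction, as expected with no shift.
- D = 20, L = 14, life-saving drug: significantly shorter in 10%, with a mean shift of -0.38 days after the day-30 cap.

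The same algebra applies to oxygen and ventilation days with their own D, L and S. No numbers were put to those.

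**The case against.** **The model is unnamed and the SAP is not shown.** The protocol does not say linear regression, means or survivors only, and an SAP may add a rule for death. This stands in part: it cannot be stated as fact that deaths will be scored as early discharges. The protocol does more than stay silent, however. It defines two event times, moves them to a day scale, and keeps its time-to-event model for two other outcomes.

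**The direction is not fixed.** A reader might infer that the plan gives the wrong sign whenever the primary hypothesis is true. The documents do not support that. The protocol gives no timing of death or discharge. The shift vanishes when D = L and reverses when deaths come later. A survivors-only analysis shows none when L = S. Scoring deaths as 30 days, which the protocol does not exclude, favours the life-saving drug. The primary hypothesis also concerns mortality only, so it sets no true sign for stay. If the drug also shortened every survivor's stay by one day, the treated mean would fall by 0.925 x 1 = 0.93 days. That outweighs a shift of +0.45, roughly cancels +0.90, and is outweighed by +1.50.

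**Adjustment may absorb part of the shift.** The simulation was unadjusted, while the plan adjusts for stratum, age and comorbidities. This stands as a limit on the size.

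**Change of clock.** A reader might also see a contradiction between times from randomization and plain days of hospitalization. The latter reads naturally as shorthand for the defined outcome, so no weight is put on it.

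**Conclusion.** The concern holds in a limited form. The protocol defines discharge and end of oxygen as event times, plans to compare them, and ventilation days, as quantities, and gives no place to death or to stays past day 30. With 15% v 7.5% mortality, counting days to death biases the comparison unless D and L happen to match. Restricting to survivors biases it unless those saved stay as long as other survivors.

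If deaths come early (day 8) and typical survivors' stay is unaffected, counting to death makes a life-saving drug look about 0.45 to 1.50 days longer. With late deaths the shift is zero or negative. These sizes rest on assumed D, L and S, and the rejection rates also on an assumed spread and no adjustment. The sign cannot be settled from the protocol. The outcomes are secondary and the primary mortality comparison is unaffected, so this should be changed but does not threaten the trial's main result.

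**What to change.** In the statistical analysis paragraph of section 3.4, take hospital and oxygen days out of the day-count model.

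- Analyse discharge alive and off oxygen alive, from randomization to day 30, as time-to-event outcomes with death as a competing event. A death never counts as discharge or recovery: the patient stays classed as not discharged, or not off oxygen, to day 30.
- Censor at day 30 those still in hospital or on oxygen.
- Compare cumulative incidence between arms, keeping the stratum and the same covariates.
- As the day-scale summary, report hospital-free, oxygen-free and ventilator-free days to day 30 with death scored 0. This also closes the gap for ventilation days.

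The cost is protocol or SAP wording, with the same data and the same 30-day follow-up. The downside is in interpretation: the main result is a probability or rate of being discharged alive, not a difference in mean days.
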